### Data collection instruments / outcome measures

Unless otherwise indicated, all study measures have established validity and reliability, and are widely available. Specific study measures are available from the corresponding author.

#### Primary outcome measure

Child emotional and behavioural wellbeing will be measured by the *Strengths and Difficulties Questionnaire* (SDQ [33];), which is a routinely used clinical tool completed by caregivers and designed to assess emotional and behavioural difficulties in children aged between 3 and 17 years. It was used in the preliminary evaluation and feasibility study [31] and is recognised as the UK government’s preferred measure of wellbeing for children in care. The SDQ consists of 25 closed-ended questions and an impact supplement, which assesses the extent to which mental health problems have had an impact on aspects of the child’s life. Each item is rated using response categories of ‘Not-true’, ‘Somewhat true’, and ‘Certainly true’. The 25 items are scored across five (five-item) subscales: *Conduct problems, Emotional problems, Hyperactivity, Peer problems,* and *Prosocial.* For all the subscales, apart from the prosocial subscale, higher scores are designed to indicate that there are greater levels of difficulty. A total difficulties scale is generated by summing all of the scales except for the prosocial scale.

#### Secondary outcome measures

Parental stress will be measured using the *Parenting Stress Index – Short Form* (PSI 4-SF; [34]), which is a self-report measure comprising 36 items using a 5-point Likert scale; designed to assess perceived stress in the parenting role. The 36 items are divided into three 12-item subscales; Parental distress, Parent-child dysfunctional interaction, and Difficult child, which combine to form a total perceived stress score. Higher scores on these scales, and on the total stress score, are meant to reflect greater difficulties, with a score of 90 and above (on both the total score and subscales) falling within the ‘clinical’ range.

*The Parental Reflective Functioning Questionnaire* (PRFQ; [37]) will be used to measure the carers’ capacity for reflective functioning in their caregiving role. The PRFQ is an 18-item questionnaire including three main subscales: *Pre-mentalizing,* which assesses non-mentalizing of the child, or inability of the parent to acknowledge their child’s mental states; *Certainty about mental states*, which measures how certain caregivers are about the mental states of their child and their ability/inability to recognise the opacity of mental states; and *Interest and Curiosity*, which is designed to measure parental interest and curiosity in their child’s mental states.

High scores in Pre-mentalizing and Certainty about mental states reflect reduced capacity for reflective functioning, and high scores in Interest and Curiosity represent increased reflective functioning.

*The Professional Quality of Life Questionnaire* (PRoQOL) [35] will be used to measure foster carer compassion fatigue and burnout. The PRoQOL is a 30-item self-report measure of the positive and negative effects of working with people who have experienced extremely stressful events. Items are scored using a Likert-type scale where 1 = Never and 5 = very often. The PRoQOL contains three subscales measuring Compassion Fatigue, Burnout and Compassion Satisfaction.

*The Emotion Regulation Checklist* (ERC; [36]) will be used to assess the carer’s view of a child’s emotions. The ERC consists of 24 items scored using a 4-point Likert-type scale, where 1 = Never and 4 = Always, designed to be completed by an adult who knows the child well, such as a parent or carer. The measure has two subscales: *Lability/Negativity* (15 items), which is designed to assess emotional intensity, expression of negative emotions, arousal and reactivity, and lability of mood, and *Emotion regulation* (8 items), which measures adaptive regulation, such as socially appropriate displays of emotion, empathy and emotional understanding. Higher scores on the *Lability/Negativity* scale reflect greater dysregulation, whilst higher scores on the *Emotion regulation* scale indicate a higher capacity for emotion regulation.

*Carer-Defined Problems Scale* (CDPS; [38]) is a measure adapted from the Goal-Based Outcome Measure (GBO; [43, 44]). The measure asks carers to rate and record up to three problems at the beginning of the intervention (‘Please List below, in order of priority, three problems you have with your child that you would most like help with. Then rate the severity of the problem at present by indicating a number from 0 to 10’). In this version, adapted for online use, changes on the scale are rated by participants on a scale from 0 (no longer a problem) to 10 (couldn’t be worse). The outcome is the amount of movement along the scale from the start to the end of the intervention. Evidence from Briskman and colleagues (2012) has indicated that this measure is highly sensitive to change for foster carers reporting on identified problems with the ‘target’ children they are considering in relation to a parenting-based intervention [45].

The *Placement Stability Log* has been developed for use in this study and will be used to collect data relating to changes of social worker, change of school or placement change and reasons for any change. The Placement Stability Log asks carers to report when there has been any significant events or changes relating to the child’s placement. It asks about any changes to the child’s foster placement and if so, where to and the reasons why. Lastly it asks about foster child-related events.

Data from this measure will be used to track placement stability and inform collection of follow-up measures, e.g. if a child has moved placement.

#### Economic evaluation measures

##### Child Health Utility 9 Dimensions (CHU9D) [40]

A paediatric generic, preference-based measure of health-related quality of life, to be completed by the carer. The CHU9D covers nine dimensions (worried, sad, annoyed, tired, pain, sleep, daily routine, work, able to join in activities), each rated on five levels, and can be used to generate quality-adjusted life years (QALYs) for use in cost-utility analysis.

##### Child and Adolescent Service Use Schedule (CA-SUS)

Service-use data will be collected using an adapted version of the CA-SUS, a measure originally designed for young people in mental health populations, but which has been adapted and successfully implemented in a range of health and social care-based studies [46, 47]. The version we will use was designed and tested for use with children in care in an earlier feasibility study [39, 48] and an online, self-report version is now being developed. The CA-SUS will be completed remotely by carers at baseline, covering the previous 3 months, and at both follow-ups (4- and 12-months post-baseline), covering the period since last assessment. The CA-SUS will be reviewed at the end of the Pilot Phase and has been adapted to ensure coverage of remote online and telephone delivery of services, given the changes to service delivery as a result of Covid-19 restrictions.

#### Other measures

##### Foster carer demographics form

Basic demographic information about foster carers will be collected at baseline using the *Foster carers demographics form*. This 15-item questionnaire will ask foster carers to provide information about themselves (e.g. Age, gender, ethnic background, educational history and marital status), their fostering history, and demographic and fostering history of the child in their care.

##### Fostering team site profile questionnaire (SPQ)

Service characteristics of local authorities will be collected at the beginning and end of the trial period via a *Fostering team site profile questionnaire*. This 16-item questionnaire will gather information which characterises services, including numbers of children placed in foster care, numbers of registered foster carers, and associated interpreting services, and existing foster caring policies, training, and support programmes in place. Data from this measure will allow researchers to identify changes in the service between pre- and post-intervention.

#### Facilitator evaluation

As part of the embedded process evaluation (see below), facilitator adherence will be measured using the Reflective Fostering Programme *Facilitator Adherence Rating (FAR)* (Unpublished tool): a 14-item observation-based assessment, covering the key components of the Reflective Fostering Programme, used to assess facilitators’ adherence to the Programme.

#### Interview schedule (Foster carer interviews)

An interview schedule will be used to guide semi-structured interviews with foster carers as part of the process evaluation. The interview schedule will include the following topics:
Experience of being a foster carerExperience of receiving the intervention/usual supportThe Reflective Fostering Programme (Intervention arm only)The type of fostering support received (control arm only)Wider experiences of taking part in the study

Topics and discussions may vary slightly depending on what group the foster carer was allocated to. Interviews are expected to take no longer than 1 h.

#### Topic guide (focus groups with facilitators)

Focus groups with facilitators will take place to understand experiences of programme delivery, including co-delivery by carers and social workers, and how the wider context of local authorities influenced intervention delivery. A topic guide has been developed to elicit conversation and ensure all essential topics are covered in the focus group. Topics to be covered include:
Facilitator experiences of delivering the ProgrammeUsefulness of the Reflective Fostering Programme trainingThe Reflective Fostering ProgrammeExperiences of co-deliveryWeekly supervisionWider experiences of taking part in The Reflective Fostering Study

Focus groups are expected to take no longer than 1.5 h.

### Plans to promote participant retention and complete follow-up {18b}

All participants will be provided with a unique username and password so they can sign into the database and complete the study measures. Foster carers will be automatically reminded by text, email, or phone call to complete the assessments by the research team, and will be followed up in the same way, if necessary, to encourage completion. Those participants unable to complete the study measures online will complete these with a member of the research team by telephone. If they cannot be completed by telephone, participants will be provided with paper copies to complete and return (if COVID-19 restrictions allow). This will ensure that participants who might not be confident in using technology will still be able to complete the measures.

Participants who withdraw from the intervention will be asked to continue to provide outcome data. For participants who discontinue with the study itself, a study withdrawal form will be completed detailing how the participant communicated their wishes to withdraw, type of withdrawal, date, reasons (if obtained), and any discussion regarding withdrawal.

### Data management {19}

Data will be entered under each participant’s Participant ID (PID) onto the central database, stored on servers based at NCTU by members of the study team working within each research site, and collected at the time-points indicated in the Trial Schedule. Randomisation of participants will also be implemented within this database.

Data collection, data entry, and queries raised by a member of the study team will be conducted in line with the NCTU and study-specific data management processes. Identification logs, screening logs, and enrolment logs will be kept at the study site in a locked cabinet within a secured room. Electronic copies of these logs will be kept on the Investigator Site Files which will be password protected. All data will be handled in accordance with the Data Protection Act 2018.

Access to the database will be via unique, individually assigned (i.e. not generic) usernames and passwords. The database will be accessible only to members of the study team, and external regulators if requested. Functional access within the database will be controlled and limited by role and, where appropriate, by site. This access to the study database is controlled and administered by NCTU Data Management. The servers are protected by University of East Anglia (UEA) firewalls and anti-virus products and are patched and maintained (including back-ups) according to best practice. The physical location of the servers is environmentally controlled and protected by CCTV and security door access.

Participant identifiable data will be stored in the database to enable participants to be contacted by site staff for the purpose of sending questionnaires. There will be a clear logical separation of participant identifiable data from the trial data (i.e. by user/role permissions and by data collection instrument).

The database software provides a number of features to help maintain data quality, including maintaining an audit trail, allowing custom validations on all data, allowing users to raise data query requests, and search facilities to identify validation failure/ missing data.

After completion of the study, the database will be retained on the servers of NCTU for on-going analysis of secondary outcomes. The study database and associated design documentation will be routinely archived for a period of 5 years unless otherwise advised by the Trial Management Group (TMG). Note that all identifying information such as email addresses will be removed prior to archiving.

### Confidentiality {27}

Confidentiality and anonymity will be ensured throughout the study. For those in the intervention arm, participants may discuss sensitive matters during recorded sessions, and any participants may discuss sensitive matters during interviews or focus groups. This will be managed through close attention to confidentiality. The reporting of results (including quotations) will be fully anonymised and excerpts will only be used with the explicit consent of participants.

The study staff will ensure that the participants’ anonymity is maintained. The participants will be identified only by a Participant ID number on all study documents and any electronic database. Additionally, participant identifiers required for automated communication (including email address and mobile telephone number) will also be stored in the database, but logically separated from study data by interface and permission constraints. All documents will be stored securely and only accessible by study staff and authorised personnel. The study will comply with the Data Protection Act 2018, which requires data to be anonymised as soon as it is practical to do so.

Following the Caldicott Principles, only data to be used in analysis relevant to the study and to facilitate running the study will be collected, limited to the surveys and demographic material to be used for data analysis, and contact details for electronic communication. All participants will be identified by a unique ID code that will only be linkable to their name via a password-encrypted excel file. Only a limited number of researchers will have access to the link between participant names and ID numbers.

An electronic CRF will be produced. Each participant will have a corresponding CRFs unique to them. CRFs will not bear the participant’s name. The participant’s initials, date of birth, and study PID will be used for identification on the database. Access to the database will be managed by NCTU and will be restricted and controlled to authorised personnel and will be password protected. The audit trail will be monitored regularly for any unauthorised access. It is the responsibility of the CI/Site Lead(s) to ensure that relevant personnel are delegated to carry out data collection and data entry. The delegation log will identify all those personnel with responsibilities for data collection and handling, including those who have access to the trial database.

### Plans for collection, laboratory evaluation, and storage of biological specimens for genetic or molecular analysis in this trial/future use {33}

Not applicable, no samples collected.

## Statistical methods

### Statistical methods for primary and secondary outcomes {20a}

Data collected from foster carers who were approached but chose not to participate and those who withdrew during the study will be analysed for any trends. All data collected up to the point of withdrawal of consent will be retained in the study dataset and will be included in the analysis according to the intention-to-treat principle.

#### Primary analysis

A general linear model, using general estimating equations (GEE), will be used for the analysis of the primary outcome, carer-reported SDQ at 12 months. The GEE approach to estimation will incorporate the clustering in outcome values by intervention groups within the intervention arm. As there is no overt clustering in the control arm (i.e. an example of ‘partial clustering’), each participant within the control can be considered a ‘cluster of one’ for analysis purposes. The linear model will include recruiting ‘site’ (as a random effect), the SDQ score at baseline, age, and previous number of placements (design factors) and intervention group. The primary outcome, SDQ, is assumed to follow a normal distribution. The residuals from this model will be checked against this assumption. The primary analysis will use the intention-to-treat principle, i.e. analysing participants according to the group to which they were randomly allocated, irrespective of intervention received.

#### Secondary outcome analysis

Secondary outcomes, including the SDQ at 4 months, will be analysed in a similar fashion, i.e. through a linear model using GEE with an appropriate link and error term depending upon the nature of the outcome. No subgroup analyses are currently planned, but should the need for subgroup analyses become apparent during the course of the study (for example due to new information), these will be specified in the Statistical Analysis Plan (SAP) and most likely analysed using an interaction effect in the linear model. If the study includes a mix of face to face and online delivery of the Reflective Fostering Programme, a formal subgroup analysis comparing the two will be applied. This will involve the addition of a group-by-delivery type intervention term. However, the study has not been primarily designed to address any differences in outcome associated with delivery format.

Reflective capacity, as measured by the PRFQ, is a target of the intervention and, therefore, needs to be considered as one of the secondary outcomes. However, reflective capacity is also one of the mechanisms of change of the intervention and may be important in mediating the effect of the intervention on both the child and the foster carer. Reflective capacity will therefore be considered as both a secondary outcome and a mediating factor.

### Interim analyses {21b}

There are no planned formal interim analyses. Summaries of safety and efficacy data will be considered on a regular basis by the oversight committees.

### Methods for additional analyses (e.g. subgroup analyses) {20b}

Three potential moderators of outcome have been identified and a formal subgroup analysis will be undertaken corresponding to each. The three are (1) the foster carers reflective caring at baseline; (2) the child’s age (from 4 to 9, versus 10 to 13); and (3) the number of previous placements (none or one, versus 2 or more). In each case, the analytical model for efficacy described above will have to be extended to include an interaction term, i.e. the interaction between subgrouping variable and treatment arm. No formal sample size calculation has been carried out and the study has not been designed to provide a set level of statistical power for these subgroup analyses. Additional subgroup analyses may be suggested during the course of the study in the light of emerging information from other studies. These will be kept to a minimum and explicitly stated in the SAP.

The change in foster carer’s parental reflective functioning is proposed as a mediator of outcome, i.e. an intermediary variable on the causal pathway between intervention and primary outcome. To test this, a formal mediation analysis will be carried out using the approach suggested by Baron and Kenny [49]. This involves firstly modelling the relationship between intervention and parental reflective functioning and between parental reflective functioning and outcome (i.e. along the mediated route), plus modelling the relationship between intervention and outcome (i.e. the direct route) whilst adjusting for parental reflective functioning. This analysis will only be carried out, conditional on a significant effect of intervention being found in the primary analysis.

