### Objectives {7}

The objectives of this study are to evaluate the effectiveness, cost-effectiveness, and process of delivery of the Reflective Fostering Programme for foster carers looking after children aged 4 to 13 years. The primary aim is to establish whether adding the Reflective Fostering Programme to usual support is more effective than usual support alone, in promoting the emotional and behavioural wellbeing of children in care; reducing levels of foster carer stress and burnout; increasing foster carer parental reflective capacity; increasing foster carer quality of life and meeting their personalised goals; improving the carer-child relationship; and in reducing placement instability.

Within the main trial, an internal pilot study will assess recruitment and randomisation procedures, examine retention and data completion rates, and explore any issues of contamination across the trial arms. In addition, an integrated economic evaluation will be conducted to determine the cost-effectiveness of implementing the Reflective Fostering Programme alongside usual support compared to usual support alone.

Across the whole trial, an embedded mixed methods process evaluation will describe how the Reflective Fostering Programme and usual support are delivered, assess intervention fidelity, understand how contextual factors shape intervention delivery, and provide explanations for the observed effects of main trial findings.

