#### Secondary outcomes

Secondary outcomes are the absolute values for the SDQ at 4 months, and the following outcome measures recorded at 4 and 12 months post-baseline: foster carer’s level of stress as measured by the Parenting Stress Index (short form) (PSI 4-SF) [34]; foster carer’s quality of life and foster carer’s compassion fatigue and burnout (Professional Quality of Life Questionnaire, PRoQOL) [35]; the Child’s capacity for emotional regulation, as measured by the Emotional Regulation Checklist (ERC) [36]; foster carer’s reflective capacity, as measured by the Parental Reflective Functioning Questionnaire (PRFQ) [37]; achievement of personalised goals set by the foster carer (measured by the Carer Defined Problem Scale (CDPS)) [38]. In addition, we will examine placement stability, which is recorded in relation to changes of social worker, change of school, or placement change, and reasons for any change. The data will be recorded using the Placement Stability Log.

See section ‘Plans for assessment and collection of outcomes {18a}’ for a more detailed description of the study outcome measures.

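### The mediation analysis runs only after a significant primary result, so the indirect effect goes unestimated when the primary is null, although an indirect effect needs no significant total effect

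*Protocol article*

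**What the plan says.** All references are to the protocol article; the statistical analysis plan is not at hand.

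- *Methods for additional analyses {20b}* names the mediator: "The change in foster carer’s parental reflective functioning is proposed as a mediator of outcome". The method is fixed: "a formal mediation analysis will be carried out using the approach suggested by Baron and Kenny". Three relationships are to be modelled: intervention with mediator, mediator with outcome, and intervention with outcome "i.e. the direct route) whilst adjusting for parental reflective functioning".
- The same paragraph ends with the condition at issue: "This analysis will only be carried out, conditional on a significant effect of intervention being found in the primary analysis".
- *Secondary outcomes* places the PRFQ among "the following outcome measures recorded at 4 and 12 months post-baseline". *Primary analysis* concerns "the analysis of the primary outcome, carer-reported SDQ at 12 months".
- *Secondary outcome analysis* treats reflective capacity both as a secondary outcome and as a mediator. Its analysis as a secondary outcome carries no significance condition.

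**The concern.** Reflective capacity is the mechanism through which the programme is meant to work. If the primary comparison is not significant, three explanations compete:

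1. Reflective capacity did not move.
2. It moved, but is unrelated to the child's outcome.
3. It moved and does matter, but the resulting effect on the child was diluted, or offset by an effect running the other way.

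The ungated PRFQ analysis addresses the first. Separating the second from the third needs the mediator-outcome path and the indirect effect, and the condition removes both in exactly the case where they are wanted.

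The statistical premise is also weak. The total effect is the sum of an indirect part (a × b, where a is the effect of arm on mediator and b the effect of mediator on outcome given arm) and a direct part c'. A non-significant sum does not show that a × b is zero. It can be small because b is modest, or because c' has the opposite sign, while a and b are each estimated precisely.

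**Working it through.** **1. How often does the condition block the analysis?** The chance that it is met is the power of the primary test, so the first step is to reproduce the protocol's own figure.

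Inputs from *Sample size {14}*: 720 randomised, 360 per arm; two-sided 5%; effect size 0.3; average group size 7; same clustering in both arms; ICC 0.05 or 0.10; drop-out 20 to 25% at 12 months. The 20% case is worked here.

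- Analysed per arm: n = 360 × 0.80 = 288. Average group size after drop-out: m = 7 × 0.80 = 5.6.
- Design effect = 1 + (m − 1) × ICC: 1 + 4.6 × 0.05 = 1.23, and 1 + 4.6 × 0.10 = 1.46.
- Standard error of the standardised difference = √(2 × design effect / n): √(2.46/288) = 0.0924, and √(2.92/288) = 0.1007.
- Power = Φ(d/SE − 1.96). At d = 0.3: Φ(3.246 − 1.96) = 90.1%, and Φ(2.979 − 1.96) = 84.6%.

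Table 2 states 90% and 85% for this case, so its figures are reproduced. The same formula gives 91.3/85.9% at 15% drop-out (stated 91/86%) and 88.6/83.1% at 25% (stated 88/83%).

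The chance that mediation is not run is 1 minus power:

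| True effect | d/SE (ICC 0.05 / 0.10) | Power | Analysis blocked |
|---|---|---|---|
| 0.4 (upper end of the protocol's clinically relevant range) | 4.328 / 3.973 | 99.1% / 97.8% | 1% / 2% |
| 0.3 (design value) | 3.246 / 2.979 | 90.1% / 84.6% | 10% / 15% |
| 0.2 (assumed) | 2.164 / 1.986 | 58.1% / 51.0% | 42% / 49% |

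Over drop-out of 15 to 25% the blocked share is 9 to 17% at 0.3 and 40 to 51% at 0.2.

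**2. Can the paths be detectable when the total effect is not?** A simulation was run with 288 per arm, residual SD of 1 for mediator and outcome, no clustering, and each path tested at 5%. The path sizes are assumptions; the protocol gives none.

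- *Full mediation*, a = 0.4, b = 0.3, c' = 0. Total effect = 0.4 × 0.3 = 0.12. Both paths were significant in over 99% of trials and the total effect in about 30%, so the rule blocks the analysis in about 70%. Check by formula: the outcome variance within arm is 1 + 0.3² = 1.09, SE = √(2 × 1.09/288) = 0.087, 0.12/0.087 = 1.38, and Φ(1.38 − 1.96) is about 28%.
- *Opposing direct effect*, a = 0.5, b = 0.3, c' = −0.15. Total effect = 0.15 − 0.15 = 0. Both paths were significant in nearly all trials, and the rule blocks about 95%.
- *Indirect and direct effects in the same direction*, a = 0.4, b = 0.3, c' = 0.18. Total effect = 0.12 + 0.18 = 0.30. The rule blocks about 6%.

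The rule therefore does little harm when the total effect is near the design value. It does most harm when the effect is diluted or offset.

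**3. Are the data for a time-ordered analysis planned?** Yes. *Secondary outcomes* lists the PRFQ at 4 and 12 months, and the primary SDQ is at 12 months, so the 4-month PRFQ can serve as a mediator that precedes the outcome.

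**The case against.** The strongest reply is that mediation is one additional analysis. Declining to look for mechanisms after a null primary limits post hoc searching, and at the protocol's own effect sizes of 0.3 to 0.4 the condition would seldom bite. The caution has some merit, and the figures at 0.2 do rest on an effect that the protocol does not state. Labelling the analysis exploratory meets the first point without discarding it. The second assumes that the programme works as hoped, and a null trial is where the question of mechanism arises.

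Several stronger readings are tempting, and the document does not support them:

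- *That the mediation models are unadjusted.* Covariates are not listed, but they are not excluded either. The direct-route model contains both arm and mediator, so its mediator coefficient is already adjusted for arm.
- *That the absence of a stated PRFQ time point or of an interval for the indirect effect is a defect.* These are details that a protocol article commonly leaves to the analysis plan.
- *That the plan forbids learning whether reflective capacity moved.* It does not, because the PRFQ is analysed as a secondary outcome whatever the primary result.
- *That the condition contradicts the aim in Objectives {7} to "provide explanations for the observed effects of main trial findings".* That aim belongs to the mixed-methods process evaluation, which has no such condition.
- *That a positive result would yield misleading mediation.* Randomisation does not protect the mediator-outcome path, so caution is fair, but the size of any bias depends on confounding about which the document gives no figures.

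Time order would not remove every difficulty. Where one unblinded carer reports both the 4-month PRFQ and the 12-month SDQ, shared-rater correlation remains.

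**Conclusion.** The point holds for the significance condition. It is an explicit rule and not an omission, and an analysis plan that follows the protocol would inherit it. It blocks the mediation analysis in about 10 to 15% of trials at the design effect of 0.3 (20% drop-out, ICC 0.05 to 0.10, clustering in both arms) and in about 42 to 49% if the true effect were 0.2, which is assumed. The simulated cases, with about 70% and 95% blocked, show that both paths can be clearly detectable behind a non-significant total effect. They depend on assumed path sizes and ignore clustering.

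What is lost after a null primary is specific: the mediator-outcome path and the indirect effect. The trial then cannot separate, in numbers, a mechanism that moved without mattering from one whose effect was diluted or offset. The primary conclusion and the secondary outcome estimates are unaffected. The change is worth making, but the validity of the main result does not depend on it.

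**What to change.** In *Methods for additional analyses {20b}*, and in the analysis plan:

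1. Delete the sentence that makes mediation conditional on a significant primary result.
2. Whatever the primary result, estimate the indirect effect with a confidence interval, for example from a bootstrap that resamples intervention groups as units (each control participant being a cluster of one, as in the primary model). Label it exploratory.
3. Use 4-month PRFQ as mediator and 12-month SDQ as outcome, so that the mediator precedes the outcome.
4. Include arm, baseline PRFQ, baseline SDQ and the design factors in the models.
5. Add a sensitivity analysis for unmeasured confounding of mediator and outcome.

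The cost is protocol and analysis-plan wording plus modest analysis time. No new data are needed, since the measures are already planned. Table 1 as available here shows no PRFQ row, so its schedule should be reconciled with *Secondary outcomes*. The downside is that an exploratory mediation result will be reported even when the primary is null, and the report must keep it from being read as evidence of effectiveness.
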